	**Intervention group**
	Standard care + CuidaCare intervention
	**Control group**
	Standard care
Step 5	Follow-up (0 months after intervention)
	Collection of variables on:
	- Dependent Patient: degree of cognitive deterioration and dependency level.
	- Evaluation of formal support.
	- Caregiver: Self-perceived quality of life, degree of burden, evaluation of anxiety/depression degree, Apgar family test, and nursing diagnosis.
Step 6	Follow-up (6 months after intervention)
	Collection of variables on:
	- Dependent patient: degree of cognitive deterioration and dependency level.
	- Evaluation of formal support.
	- Caregiver: Self-perceived quality of life, degree of burden, evaluation of anxiety/depression degree, Apgar family test, and nursing diagnosis.
	**Intervention group**
	Standard care + reinforcement of CuidaCare intervention
	**Control group**
	Standard care
Step 7	Follow-up (12 months after intervention). End of trial.
	Collection of variables on:
	- Dependent Patient: degree of cognitive deterioration and dependency level.
	- Evaluation of formal support.
	- Caregiver: self-perceived quality of life, degree of burden, evaluation of anxiety/depression degree, Apgar family test, and nursing diagnosis.

### Losses to follow-up

The number of caregivers who decline to participate in the trial will be recorded according to the requirements of the CONSORT declaration [31]; data on their age and sex will be collected. Similarly, losses to follow-up and abandonments, as well as the relevant causes, will be recorded during the study. With the intention of minimizing such losses to follow-up, caregivers will be contacted by phone to schedule the visits.

### Withdrawal criteria

Main caregivers who, once recruited, sicken of a severe pathology.

Main caregivers of dependent patients who are hospitalized for more than 3 months over the trial period.

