### Variables

#### *Outcome variables*

The main outcome variable is quality of life perceived by the caregiver, expressed on the EQ-5D VAS [20,21]. This questionnaire comprises two sections: the VAS and the descriptive system EQ-5D Dimensions. In the VAS, subjects evaluate their own health condition on a scale ranging from 0 (worst imaginable health condition) to 100 (best imaginable health condition). The EQ-5D Dimensions system contains 5 questions where 5 dimensions of HRQL (Mobility, Self-Care, Usual Activities, Pain/Discomfort, Anxiety/Depression) are evaluated. Each question has 3 possible answers ranging from 1 (I do not have difficulties) to 3 (I have many difficulties).

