### Analysis

1. Descriptive analysis of each variable with its corresponding 95% confidence interval (CI). Tests for normality. Description of the profile of patients who abandon the study, and their reason for withdrawal.

2. Comparison of the group at the beginning of the trial for response variables, descriptive variables, and prediction factors. Bivariate, statistical, and other tests appropriate for the type of variable (qualitative or quantitative) will be used.

3. Analysis of primary outcome at the end of the intervention (0 month of follow-up period), and at 6 and 12 months after the intervention. The average change in EQ-5D VAS value before and after the intervention will be compared between the two groups by using parametric and/or non-parametric tests and the CI of the difference will be calculated. A mixed-effects regression model will be used to adjust by prognostic factors. Confounding factors or factors that may alter the recorded effect will be taken into account in this analysis.

4. Analysis of secondary outcome. For each of the secondary response variables, the variable outcomes will be compared based on the assigned group by calculating the difference of means or proportions of each variable, as well as CIs.

All statistical tests will be performed as intention-to-treat. The last and baseline observations carried forward will be used for missing data. Significance will be set at p < 0.05.

Researchers in charge of performing the analysis will not know which intervention has been assigned to each of the included patients.

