## Discussion

Systematic reviews of studies [14-17] evaluating the effectiveness of interventions and caregiving strategies for the caregiver show methodological limitations in their conclusions, mainly related to insufficient sample sizes, high losses to follow-up of subjects, and follow-up period duration. They also reveal the variability of the interventions and outcome variables employed.

The CuidaCare intervention is a personal intervention, aimed at both the caregiver and the dependent patient, and based on coping techniques.

The design selected for this project is the best possible given the intervention, while seeking to avoid possible contamination effects among centers. The number of clusters is sufficient for the randomization to balance potentially confounding factors among themselves and we consider modelization techniques which take into account the intracluster correlation.

Given the nature of the intervention, it cannot be masked. However, we have designed a blind evaluation of the outcome.

Subjects will be recruited for the study by their own nurses. This increases variability, which we attempt to minimize by training all participating nurses on the one hand, and by creating a research protocol and implementing an electronic data collection notebook on the other hand.

Of note, the fact that nurses recruit their own patients increases implementation in standard practice.

Participation of nurses is voluntary. We are aware that a bias is introduced, but they are motivated and engaged professionals who will facilitate the development of innovative interventions such as CuidaCare.

Despite loses to follow-up in primary care being minimal as a result of the user's proximity to the system and the possibilities the health professional has to contact relatives and friends, we have estimated a high percentage in the trial due to the high morbidity-mortality of dependent patients, which will force the caregiver to abandon the trial due to the patient's hospitalization or death.

The design of the trial is pragmatic, which will allow evaluating not only its effectiveness, but also its applicability in the context of primary care.

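### Caregivers who become severely ill are withdrawn with no provision for further outcome measurement, so carry-forward replaces a low self-rated health score with a pre-illness one

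*Protocol article*

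**What the plan says.** Under Withdrawal criteria the protocol article lists two groups: "Main caregivers who, once recruited, sicken of a severe pathology" and "Main caregivers of dependent patients who are hospitalized for more than 3 months over the trial period". It does not say what counts as severe, or whether outcomes are still measured afterwards.

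Outcome variables defines the primary measure: "In the VAS, subjects evaluate their own health condition on a scale ranging from 0 (worst imaginable health condition) to 100 (best imaginable health condition".

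Three relevant statements stand in the Analysis section:
- "All statistical tests will be performed as intention-to-treat".
- "The last and baseline observations carried forward will be used for missing data".
- Those who leave are to be characterised: "Description of the profile of patients who abandon the study, and their reason for withdrawal".

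On timing, Concealment of allocation and Table 1 place randomisation of the centres after caregivers are chosen. The baseline visit, a 6-month intervention period and assessments at 0, 6 and 12 months then follow. Illness arising after recruitment is therefore mostly a post-randomisation event.

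The Discussion explains the expected losses by the morbidity and mortality of the dependent patients, "which will force the caregiver to abandon the trial due to the patient's hospitalization or death".

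**The concern.** Severe illness in the caregiver bears directly on self-rated health. A rule that stops measurement at that moment makes missingness depend on the value that would have been recorded, and the carry-forward rule then supplies a value from before the illness. A decline in health enters the analysis as no decline.

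This matters in this trial for three reasons. All caregivers are 65 or older and are followed for about 18 months from baseline (6 months of intervention plus 12), so some severe illness is foreseeable. The Background describes informal care as a cause of morbidity, and the intervention includes self-care content, so illness may be one route by which the intervention works or fails to work. The intervention cannot be masked, and the blinding described covers outcome measurement and analysis but not decisions to withdraw. An undefined severity threshold could therefore be applied differently in the two arms.

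**Working it through.** **1. The plan's own figure, used here only as a yardstick.** Inputs from Sample size: difference 15, SD 25, alpha 0.05 (taken as two-sided), power 80%, ICC 0.02, cluster size 15, loss 20%.
- Per group: 2 × (25 × (1.960 + 0.842) / 15)² = 43.6, rounded up to 44.
- Design effect: 1 + (15 − 1) × 0.02 = 1.28; 44 × 1.28 = 56.32.
- Loss: 56.32 / 0.80 = 70.4, rounded up to 71 per group, 142 in total. The stated size reproduces.
- With about 57 completers per group, the standard error of the difference is 25 × √(2 × 1.28 / 57) ≈ 5.3 points.

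**2. What happens to an ill caregiver's score.** Followed as written: illness, then withdrawal, then no stated further VAS, then a carried value from before the illness. If a share *w* of an arm becomes ill and the VAS falls by *D* points, the arm mean change is too favourable by *w* × *D*. For *w* = 10% and *D* = 20 to 40, that is 2 to 4 points; for *w* = 5%, it is 1 to 2 points.

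**3. Effect on the contrast.** The illness rates and the size of the fall are assumptions; the document gives neither. Further assumptions: caregivers who stay well gain 15 points from the intervention, well controls do not change, ill caregivers in either arm fall by *D*, and the baseline value is carried forward.
- Full follow-up: (1 − w_I) × 15 − w_I × D + w_C × D
- Baseline carried forward: (1 − w_I) × 15
- Bias: (w_I − w_C) × D

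| Ill, intervention / control | Fall *D* | Full follow-up | Baseline carried | Bias |
|---|---|---|---|---|
| 10% / 5% | 20 | 12.5 | 13.5 | +1.0 |
| 10% / 5% | 30 | 12.0 | 13.5 | +1.5 |
| 10% / 5% | 40 | 11.5 | 13.5 | +2.0 |
| 5% / 10% | 20 | 15.25 | 14.25 | −1.0 |
| 5% / 10% | 30 | 15.75 | 14.25 | −1.5 |
| 5% / 10% | 40 | 16.25 | 14.25 | −2.0 |
| 10% / 10% | 20 to 40 | 13.5 | 13.5 | 0 |

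A shift of 1 to 2 points is 7% to 13% of the 15-point target (1/15 to 2/15) and about 0.2 to 0.4 standard errors (1/5.3 to 2/5.3).

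**4. A limit of the zero.** It belongs to baseline carry-forward under these assumptions. If the last value is carried instead, and it was recorded after the intervention, ill intervention caregivers keep their 15 points. With 10% ill in both arms the contrast is then 0.9 × 15 + 0.1 × 15 = 15.0 against 13.5, or 1.5 points too high. The article names both carry-forward rules without saying when each applies.

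**The case against.** The strongest reply is that nothing here contradicts intention-to-treat. Withdrawal criteria does not remove anyone from the analysis set, and the Analysis section imputes missing values and describes leavers separately. The natural reading is that withdrawn caregivers are analysed in their randomised arm. That stands. A reader might infer that the trial will compare only caregivers who stayed healthy, or that the intention-to-treat claim is false, but the document does not say so. What remains is that retention is nominal: the caregiver is counted, but the score is not theirs at that time.

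A reader might also infer that the 10 programmed CuidaCare visits make severe illness more likely to be noticed in the intervention arm. The document does not establish this. Control patients also receive the home consultation service, caregivers are recruited by their own nurses, and both arms share the same assessments. With 10% truly ill in both arms and a 30-point fall, a 1.5-point distortion needs half the illness in one arm to go unrecognised (3.0 − 1.5), which is a strong assumption. Unequal application remains possible, because the threshold is undefined and the trial is unmasked, but it is not shown.

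The patient-hospitalisation criterion is a different case: it is not caregiver ill health, and its link to the VAS is indirect. The 20% loss allowance and the Discussion show that such losses were foreseen, although an allowance of this kind protects power and does not prevent bias.

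Finally, the full protocol may provide for measurement after withdrawal. The Discussion's remark about abandoning the trial suggests otherwise, but it concerns the patient's hospitalisation or death, not the caregiver's illness.

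**Conclusion.** The point holds in a limited form. As written, the plan withdraws caregivers for an event that bears directly on the primary outcome, provides for no later measurement, and substitutes a pre-illness score. Arm means are then too favourable whenever severe illness occurs. Bias in the contrast is conditional: about 1 to 2 points under baseline carry-forward if illness differs by 5 percentage points between arms, in either direction, and about zero if illness is equal and the baseline value is carried. These sizes rest on assumed illness rates and an assumed 20 to 40 point fall. They are small beside the 15-point target and the sampling error. The reason to act is that an uncollected VAS cannot be recovered at analysis, while collecting it costs little.

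**What to change.** Add to Withdrawal criteria that meeting a criterion does not end outcome follow-up. Where the caregiver consents, collect the VAS at the scheduled 0-, 6- and 12-month visits, analyse these caregivers in their randomised arm with the observed values, and report the events and their timing by arm. State what counts as severe for the purpose of recording. Apply the same continued follow-up to the patient-hospitalisation criterion. Whether the intervention visits continue is a separate clinical matter on which no position is taken.

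The cost is a change of wording, a few more completed follow-up visits and slightly more outcome variance. Telephone collection should not be treated as already available: Losses to follow-up plans calls only to arrange visits, and data are collected by clinical interview, so a VAS taken by phone would be a new mode that needs its own provision.

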### Analysis

1. Descriptive analysis of each variable with its corresponding 95% confidence interval (CI). Tests for normality. Description of the profile of patients who abandon the study, and their reason for withdrawal.

2. Comparison of the group at the beginning of the trial for response variables, descriptive variables, and prediction factors. Bivariate, statistical, and other tests appropriate for the type of variable (qualitative or quantitative) will be used.

3. Analysis of primary outcome at the end of the intervention (0 month of follow-up period), and at 6 and 12 months after the intervention. The average change in EQ-5D VAS value before and after the intervention will be compared between the two groups by using parametric and/or non-parametric tests and the CI of the difference will be calculated. A mixed-effects regression model will be used to adjust by prognostic factors. Confounding factors or factors that may alter the recorded effect will be taken into account in this analysis.

4. Analysis of secondary outcome. For each of the secondary response variables, the variable outcomes will be compared based on the assigned group by calculating the difference of means or proportions of each variable, as well as CIs.

All statistical tests will be performed as intention-to-treat. The last and baseline observations carried forward will be used for missing data. Significance will be set at p < 0.05.

Researchers in charge of performing the analysis will not know which intervention has been assigned to each of the included patients.

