**Methods/Design:**

A community clinical trial is proposed, with a 1-year follow-up period, that is multicentric, controlled, parallel, and with randomized allocation of clusters in 20 health care centers within the Community of Madrid. The study's objective is to evaluate the effectiveness of a standard care intervention in primary health care (intervention CuidaCare) to improve the quality of life of the caregivers, measured at 0, 6, and 12 months after the intervention.

One hundred and forty two subjects (71 from each group) ≥65 years, identified by the nurse as the main caregivers, and who provide consent to participate in the study will be included.

The main outcome variable will be perceived quality of life as measured by the Visual Analogue Scale (VAS) of EuroQol-5D (EQ-5D). The secondary outcome variables will be EQ-5D Dimensions, EQ-5D Index, nursing diagnosis, and Zarit's test. Prognostic variables will be recorded for the dependent patient and the caregiver.

The principle analysis will be done by comparing the average change in EQ-5D VAS value before and after intervention between the two groups. All statistical tests will be performed as intention-to-treat. Prognostic factors' estimates will be adjusted by mixed-effects regression models. Possible confounding or effect-modifying factors will be taken into account.

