### Hypothesis

A standard care intervention (intervention CuidaCare) in primary care is more effective than standard practice for improving the quality of life of old caregivers, as measured by the EQ-5D VAS, increasing the average pre- and post-intervention score change by ≥15 points between the intervention and control groups.

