### Objectives

The objective of this study is to evaluate the effectiveness of a standard caregiving intervention (intervention CuidaCare) in primary care to improve the quality of life of main caregivers >65 years, as measured by the EQ-5D VAS during follow-up visits at 0, 6, and 12 months after the intervention.

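### Three analysis visits for the primary outcome at an unadjusted 0.05 and no visit named as primary, although the trial is sized for one comparison

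*Protocol article*

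**What the plan says.** The outcome itself is clear. Under Outcome variables: "The main outcome variable is quality of life perceived by the caregiver, expressed on the EQ-5D VAS".

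The time of the primary comparison is less clear:

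- Objectives: quality of life "as measured by the EQ-5D VAS during follow-up visits at 0, 6, and 12 months after the intervention". Three visits are listed and none is singled out.
- Analysis, third item: "Analysis of primary outcome at the end of the intervention (0 month of follow-up period), and at 6 and 12 months after the intervention". A comparison of mean change between the groups follows. The mixed-effects model is described as a means of adjusting for prognostic factors, not as one test over all visits.
- Analysis, closing paragraph: "Significance will be set at p < 0.05". This is the only statement on the level of the tests.
- Hypothesis: "increasing the average pre- and post-intervention score change by ≥15 points between the intervention and control groups". No visit is given.
- Abstract, Methods/Design: "The principle analysis will be done by comparing the average change in EQ-5D VAS value before and after intervention between the two groups". Again no visit is given; 0, 6 and 12 months appear there only as measurement times.
- Sample size: one post-intervention difference of 15 points, SD 25, alpha 0.05, power 80%, and an allowance of 20% attrition over one year.

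Table 1 (Data collection method) gives a 6-month intervention period and then the three follow-up visits. For the intervention group, Step 6 lists "Standard care + reinforcement of CuidaCare intervention".

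**The concern.** A primary outcome needs a time as well as a scale. Here the scale is fixed, but three times are attached to it, each under the same unadjusted level. The calculation behind 142 allows for one test. If the results differ between visits, the protocol gives no basis for saying which one decides the trial, and the choice could be made after the data are seen. A significant result at any one visit could then be reported as the primary result, with a false-positive rate above the nominal 5%. The 15-point difference for which the trial is powered would also not be tied to a particular visit.

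**Working it through.** **1. The plan's own figure.** Inputs from Sample size: difference 15, SD 25, alpha 0.05 (taken as two-sided; the section does not say), power 80%, intraclass correlation 0.02, 15 caregivers per cluster, 20% attrition.

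- n per group = 2 × (1.960 + 0.842)² × (25/15)² = 43.6, rounded up to 44.
- Design effect = 1 + (15 − 1) × 0.02 = 1.28.
- 44 × 1.28 = 56.32; 56.32 / (1 − 0.20) = 70.4, rounded up to 71 per group, 142 in total.

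The stated figures reproduce exactly, as one two-sided test at 0.05.

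**2. Which visit does that one test refer to?** The Hypothesis and Sample size sections speak of a post-intervention comparison, which fits the visit at the end of the intervention (0 months). The one-year attrition allowance fits a later visit: with a 6-month intervention, one year from baseline is the 6-month visit, and one year from the end of the intervention is the 12-month visit. The text supports more than one answer.

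**3. Error if any visit may count.** With three independent tests, the chance of at least one false positive is 1 − 0.95³ = 14.3%. Visits on the same caregivers are correlated, which lowers this. The protocol gives no correlation, so the range below is an assumption. Each correlated figure is the probability that the largest of three equicorrelated standard normal statistics exceeds 1.96 in absolute value (simulation, 2,000,000 draws).

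| Assumed correlation between visit statistics | Chance of at least one false positive |
|---|---|
| 0 | 14.3% |
| 0.3 | 13.6% |
| 0.5 | 12.5% |
| 0.7 | 11.0% |
| 0.8 | 9.8% |
| 0.9 | 8.4% |
| 0.95 | 7.4% |

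A correlation of 0.5 is a natural reference point. Suppose all visits, baseline included, have equal variance σ² and equal correlation ρ. Each change from baseline then has variance 2σ²(1 − ρ), and two changes have covariance σ²(1 − ρ), so they correlate at 0.5 whatever ρ is. Carrying observations forward, as the Analysis section plans for missing data, pushes the correlation up and the error down, but even at 0.95 it stays above 5%.

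**4. What each remedy costs.**

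- One named primary visit: alpha stays at 0.05 and the total stays at 142. With 71 × 0.8 / 1.28 = 44.4 effective caregivers per group, power is about 81%.
- Any of three visits may count, with Bonferroni: alpha per visit is 0.05 / 3 = 0.0167, so n = 59 per group before inflation; 59 × 1.28 / 0.8 = 94.4, rounded up to 95 per group, 190 in total. If 142 is kept, power per visit falls to about 67%.

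**The case against.** The strongest reply is that the protocol leans towards one comparison. The hypothesis is a single change score, the abstract's principal analysis is a single before-and-after change, and the sample size uses a single difference. A reader could reasonably take 0 months as the intended visit. It can be added that no success rule is stated, and that a multiplicity method is often left to an analysis plan, which is not available here.

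Part of this stands. It would be wrong to say that the abstract sets out three primary tests, or that the protocol declares success at any visit. The inflation is conditional: it does not arise if one visit decides, if all three must be significant, or if one joint test is used. But the protocol adopts none of these. Nor is it silent on timing: Objectives and Analysis both give three visits for the primary outcome, under one unadjusted level. The time of the primary comparison belongs with the sample size, and the one-year attrition allowance prevents a firm reading of 0 months.

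Four stronger readings may tempt a reader, and the document does not support them:

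- *The error rate is 14.3%.* That is the independence figure, and changes that share a baseline are not independent.
- *The powered effect is undefined.* It is defined as 15 points with SD 25. Only its visit is open.
- *Inflation from ignored clustering should be added.* That is a separate question, and the Discussion says that the modelling will take account of intracluster correlation.
- *The reinforcement in Step 6 contradicts the timing of the last visit.* Table 1 shows it openly, and the visits can be counted from the end of the 6-month intervention period. It affects what the last visit measures, not the type I error.

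**Conclusion.** The point holds as a failure to designate the primary visit. The protocol attaches three visits and one unadjusted 0.05 to an outcome for which it sized a single test, and its other sections point to different visits. If significance at any visit is allowed to count, the family-wise error is about 7% to 14%. This rests on two assumptions: the any-visit rule, which is an inference from the absence of any other rule, and the correlation between visits, which the document does not give. The sample size arithmetic is correct and need not change. The point matters because the trial's main conclusion depends on which visit is read as primary.

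**What to change.** State in Objectives, Sample size and Analysis which visit is primary. The 0-month visit fits the hypothesis and the post-intervention sample size best, but the choice is the sponsor's. Make the other two visits secondary, for example tested in a fixed sequence, each at 0.05 and only if the one before it is significant. Say how the one-year attrition allowance relates to the chosen visit. When the last visit is interpreted, note that Table 1, Step 6 lists reinforcement of the intervention, so a 12-month difference need not reflect the persistence of the initial programme alone.

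This takes one or two sentences. The total stays at 142 and the chosen visit loses no power. The downside is that the sponsor must commit to one visit before seeing results. If the sponsor prefers to let any visit count, an adjustment is needed, at the cost in numbers or power worked out above.

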### Sample size

Sample size has been calculated considering a relevant post-intervention average difference of 15 points between the intervention and control groups measured on the EQ-5D VAS, and a standard deviation of 25 (estimation obtained from Roset et al. [26]). This difference is equivalent to an effect size of 0.6.

Assuming an alpha error of 0.05 and a beta error of 20%, 44 caregivers are necessary for each group.

Since randomization is done by clusters, the sample size is adjusted in order to take into account the design effect. We have considered an intraclass correlation coefficient of 0.02 [27] and assumed an average cluster sample size of 15 caregivers. The design effect is 1.28. With these assumptions and expecting a 20% loss to follow-up after a 1-year period, the required sample size is 142 (71 caregivers per group).

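### The trial is sized on a post-intervention VAS difference with SD 25 but tested on raw change, so the 80% power depends on an unstated baseline to follow-up correlation; naming baseline VAS as a covariate is never less precise.

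*Protocol article*

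**What the plan says.** **Sample size** (protocol article) bases the calculation on a "relevant post-intervention average difference of 15 points between the intervention and control groups measured on the EQ-5D VAS, and a standard deviation of 25", and adds: "This difference is equivalent to an effect size of 0.6". It continues: "Assuming an alpha error of 0.05 and a beta error of 20%, 44 caregivers are necessary for each group". It then applies an intraclass correlation of 0.02 with 15 caregivers per cluster (design effect 1.28) and 20% loss to follow-up, and reaches 142 caregivers, 71 per group.

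**Hypothesis** puts the same 15 points on the change scale: "increasing the average pre- and post-intervention score change by ≥15 points between the intervention and control groups".

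**Analysis, item 3**, gives the primary comparison: "The average change in EQ-5D VAS value before and after the intervention will be compared between the two groups", by parametric and/or non-parametric tests, at the end of the intervention and 6 and 12 months later. The Abstract calls this comparison of change the principal analysis. Item 3 then adds a mixed-effects model to adjust for prognostic factors, without naming baseline VAS among them.

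**Table 1** shows self-perceived quality of life collected at the baseline visit, so baseline VAS will be available.

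**The concern.** The sizing and the test are worded on different scales. A comparison of follow-up scores has the variance of one VAS measurement. A comparison of changes has a variance that also depends on how strongly baseline and follow-up are correlated. The document gives no such correlation and no SD of change, so the reader cannot tell whether the beta of 20% belongs to the test that will be run.

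If the correlation is modest, the trial could miss a true 15-point benefit more often than planned. The follow-up times fall about 6, 12 and 18 months after baseline (a 6-month intervention, then 0, 6 and 12 months), so a modest correlation cannot be excluded. Neither can a high one.

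**Working it through.** **Inputs from the document.** Difference 15, SD 25, alpha 0.05 (two-sided reproduces the stated n), power 80%, intraclass correlation 0.02, 15 caregivers per cluster, 20% loss, 142 caregivers, 20 centres.

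**Assumptions.** The document gives no rho, so a range of 0.2 to 0.8 is shown. 25 is taken as the SD of a single VAS score, equal at both times, and the intraclass correlation is taken to be the same on each scale.

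**Step 1: reproduce the plan.**
- n per group = 2 × [25 × (1.960 + 0.842) / 15]² = 43.6, so 44.
- Design effect = 1 + (15 − 1) × 0.02 = 1.28.
- 44 × 1.28 = 56.32, and 56.32 / 0.80 = 70.4, so 71 per group and 142 in total.

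The arithmetic in Sample size is right.

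**Step 2: effective size and power for a follow-up score.**
- Effective n per group = 71 × 0.80 / 1.28 = 44.375.
- Power = Φ(15 / (SD × √(2 / 44.375)) − 1.96). With SD 25 this is 80.7%.

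**Step 3: the other two analyses.**
- SD of raw change = 25 × √(2(1 − rho)).
- Residual SD after baseline adjustment = 25 × √(1 − rho²).
- Ratio of adjusted to change variance = (1 − rho²) / (2(1 − rho)) = (1 + rho) / 2, which never exceeds 1. Adjustment cuts the variance by 35% at rho 0.3 and by 25% at rho 0.5.

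| rho | SD of change | Power, raw change | Adjusted SD | Power, adjusted |
|---|---|---|---|---|
| 0.2 | 31.6 | 61% | 24.5 | 82% |
| 0.3 | 29.6 | 67% | 23.8 | 84% |
| 0.4 | 27.4 | 73% | 22.9 | 87% |
| 0.5 | 25.0 | 81% | 21.7 | 90% |
| 0.6 | 22.4 | 88% | 20.0 | 94% |
| 0.7 | 19.4 | 95% | 17.9 | 98% |
| 0.8 | 15.8 | 99% | 15.0 | 99.7% |

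**Step 4: break-even for raw change.** The largest SD that still gives 80% power is 15 × √(44.375 / 2) / 2.802 = 25.2. Hence rho = 1 − (25.2 / 25)² / 2, about 0.49.

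**Step 5: cluster size implied by the plan's totals.** 142 / 20 = 7.1 caregivers per centre, or 5.68 after 20% loss. The design effect is then 1 + 4.68 × 0.02 = 1.09 and the effective n per group 51.9. Break-even falls to rho about 0.40. Raw-change power is 73.4% at rho 0.3 and 79.7% at rho 0.4; adjusted power is at least 86.4% at any rho from 0 upwards.

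**Step 6: small number of clusters.** With a t reference on 18 degrees of freedom (20 centres minus 2) and design effect 1.28, adjusted power is 76.2% at rho 0 and reaches 80% only from rho about 0.3. At rho 0.3 raw change has 61.8%. At the implied cluster size of Step 5, adjusted power at rho 0 is 82.4%.

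**The case against.** The strongest reply is that 25 may have been meant as the SD of change. The Hypothesis puts the 15 points on the change scale, and the source of the SD is not at hand. If so, sizing and test agree. This stands as a possibility, but Sample size attaches the 25 to a post-intervention difference, so a clarifying sentence is needed either way.

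Second, the mixed model may already be intended to include baseline VAS as a prognostic factor. A model of change with baseline as a covariate gives the same treatment estimate as a model of the follow-up score with baseline as a covariate. A condensed article may also leave its covariate list to a fuller document. That is fair, and the missing list is not the point here. What the article does state, in the Abstract and in Analysis, is a principal comparison of unadjusted change, and a more precise choice is available from data already collected.

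Third, rho could be high. From about 0.5 upwards raw change has more than 80% power on the plan's own inputs. This stands in full.

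A reader might also infer that baseline imbalance is likely with about ten centres per arm. The document does not support that: randomisation is stratified by number of caregivers, the Discussion considers the number of clusters sufficient for balance, and under randomisation the change comparison is unbiased. The case for adjustment here is precision.

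**Conclusion.** The point holds as a mismatch of scale with a free improvement, not as a demonstrated lack of power. If 25 is the SD of a single VAS score, equal at both times, 80% power for the stated test requires rho of at least about 0.49 at design effect 1.28, or about 0.40 at the implied cluster size. Under the same assumptions the baseline-adjusted analysis is at least as precise at every rho.

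Two stronger readings go too far. One is that the stated beta does not apply to the planned test: that would need a known low rho and certainty that 25 is a single-score SD, and the document gives neither. The other is that adjustment secures 80% power: with 18 degrees of freedom and design effect 1.28 it does so only from rho about 0.3. Nor does adjustment undo any dilution of the effect from carrying baseline observations forward, which Analysis also plans.

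**What to change.** - **Analysis, item 3, and Abstract:** make the mixed-effects model already planned the primary analysis, with a random effect for health centre and baseline VAS named as a covariate. Report the adjusted mean difference with its confidence interval; it still estimates the 15-point contrast.
- **Sample size:** state whether the SD of 25 refers to the VAS score or to its change. If it is the SD of change, say so and give the basis.

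No added caregivers, visits or data are needed, since baseline VAS is already collected. The cost is the wording and about one degree of freedom.
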